### Statistical analysis

Baseline characteristics of participants undergoing LTBI testing will be summarized using means and standard deviations for normally distributed continuous variables, medians and interquartile ranges for non-normally distributed variables, and frequencies with percentages for categorical variables.

To investigate if the presence of CKD alters the risk of adverse events (present/absent) during TPT, logistic regression models will be built, initially categorizing CKD as a binary variable (present/absent) and then as a ternary variable (present severe, present and not severe, absent). The minimal sufficient adjustment set for inclusion in adjusted models will be derived from a directed acyclic graph (DAG). Potential effect modification by CKD treatment will be explored amongst individuals with CKD. All statistical analyses will be performed using R or SPSS software. Additional analyses will be considered further categorizing the outcome, e.g., on the basis of adverse event severity (ordinal logistic regression) or taking into account the association between an adverse event and the drugs in use. P-values will be corrected for multiple testing.

Assessment of the association between CKD and TPT completion will take place similarly, as will progression to active TB, albeit here using time-to-event models. Finally, the cascade of care analysis will be descriptive.

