### Sample size calculation

CKD was defined according to the Kidney Disease: Improving Global Outcomes (KDIGO) guidelines as an estimated glomerular filtration rate (eGFR) <60 mL/min/1.73 m² for at least 3 months or evidence of kidney damage.[7] This study will evaluate whether CKD, a major medical high-risk condition for TB, is associated with adverse events during TPT. It is anticipated that approximately 40% of individuals undergoing LTBI testing will be LTBI-positive and initiate TPT, of whom about 15% will have CKD. Assuming adverse event rates of 20% in the CKD group and 10% in the non-CKD group, a total of 548 TPT initiators will be required to detect this difference with a two-sided α of 0.05 and 80% power.

Based on an expected LTBI positivity rate of 40%, approximately 1,370 LTBI testing candidates need to be enrolled to yield a sufficient number of treatment initiators. This sample size will provide adequate statistical power to assess whether CKD is an independent risk factor for adverse events during TPT. A total target enrollment of 1,370 participants is planned, with competitive enrollment implemented across participating sites; per-site recruitment targets may be adjusted accordingly.

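### The sample size is an unadjusted two-group calculation, yet it is offered as adequate power for an independent CKD effect; 548 initiators give about 71% power even without adjustment

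*Protocol article*

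**What the plan says.** The Sample size calculation gives five inputs and one result. The rates and the total are: "Assuming adverse event rates of 20% in the CKD group and 10% in the non-CKD group, a total of 548 TPT initiators will be required". The error rate and power are: "to detect this difference with a two-sided α of 0.05 and 80% power". The allocation comes from the share of treated participants with CKD: "of whom about 15% will have CKD". No covariate, R² or adjusted odds ratio appears. The 548 is divided by 40% to give 1,370 enrolled.

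The following paragraph turns this into a claim about the adjusted question: "This sample size will provide adequate statistical power to assess whether CKD is an independent risk factor for adverse events during TPT".

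The Statistical analysis section says how that question will be answered. Adverse events during treatment are modelled by logistic regression on CKD, first as present or absent. For adjustment: "The minimal sufficient adjustment set for inclusion in adjusted models will be derived from a directed acyclic graph (DAG)". The Introduction makes the association of CKD with adverse events the primary objective.

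**The concern.** The test that was sized and the test named in the power claim are different. A two-proportion calculation describes the unadjusted CKD contrast. An independent effect is the CKD coefficient after adjustment.

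Confounders chosen from a causal diagram are expected to be associated with CKD, and the cohort enrols by conditions such as diabetes, autoimmune disease and malignancy (Table 1). When covariates predict CKD, the variance of its coefficient rises by about 1/(1 − R²), where R² is the share of CKD variation that they explain. Confounding can also move the effect itself. The sample size section deals with neither.

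The claim matters because the study is meant to inform national policy on the safety of preventive treatment. A non-significant adjusted odds ratio, read beside a statement of adequate power, could be taken as evidence that CKD adds no independent risk. The protocol does not say it will be read that way, but the sentence makes that reading easy.

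**Working it through.** **Inputs from the Sample size calculation.** Rates p₁ = 0.20 (CKD) and p₂ = 0.10 (no CKD); CKD share 0.15; two-sided α = 0.05 (z = 1.960); power 80% (z = 0.8416); N = 548, which is 82.2 with CKD and 465.8 without.

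**Step 1: reproduce 548.** I use the pooled two-proportion formula for the CKD group, with k = 0.85/0.15 non-CKD participants per CKD participant.

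- Pooled rate: 0.15 × 0.20 + 0.85 × 0.10 = 0.115.
- Null term: √[0.115 × 0.885 × (1 + 1/k)] = √(0.101775/0.85) = 0.3460.
- Alternative term: √[0.20 × 0.80 + 0.10 × 0.90/k] = √0.17588 = 0.4194.
- n(CKD) = (1.960 × 0.3460 + 0.8416 × 0.4194)² / 0.10² = (0.6782 + 0.3530)² / 0.01 = 106.3.
- Total = 106.3/0.15 = 708.9, so 709.

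The stated 548 is not reproduced. Other two-sided versions at 80% power give 653 (Wald log odds ratio), 764 (arcsine), 785 to 787 (continuity-corrected) and 920 (unpooled). One-sided pooled gives 567. By the pooled formula, 548 is close to the size for 70% power (538), or would fit a CKD share of about 21%. The document supports neither.

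**Step 2: unadjusted power at 548.** Power = Φ[(0.10 × √82.2 − 0.6782)/0.4194] = Φ(0.545) = 70.7%. The Wald log odds ratio gives 72.8%.

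**Step 3: adjustment with the effect held at 20% versus 10%.** Replace 82.2 by 82.2 × (1 − R²), and divide 708.9 by (1 − R²). The protocol gives no R², so this range is an assumption.

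| Assumed R² | Power at 548 | Initiators for 80% |
|---|---|---|
| 0 (unadjusted) | 70.7% | 709 |
| 0.05 | 68.8% | 747 |
| 0.10 | 66.8% | 788 |
| 0.20 | 62.4% | 887 |
| 0.30 | 57.6% | 1,013 |

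If the stated 80% were granted for the unadjusted test, Φ[2.8016 × √(1 − R²) − 1.960] gives 78.0%, 75.7%, 70.7% and 65.0% at the same four non-zero values. The mismatch would therefore remain if 548 were corrected.

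**Step 4: what 20% versus 10% means.** The unadjusted odds ratio is (0.20/0.80)/(0.10/0.90) = 2.25. The standard error of its logarithm at 548 is √{[1/(0.15 × 0.16) + 1/(0.85 × 0.09)]/548} = √(54.74/548) = 0.316. Suppose the crude rates are 20% and 10%, but positive confounding explains part of the contrast. Adjusted power is then about Φ[log OR × √(1 − R²)/0.316 − 1.960]. The adjusted odds ratios below are illustrations.

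| Adjusted OR | R² | Formula | Simulation at N = 548 |
|---|---|---|---|
| 1.95 | 0.033 | 55% | 55% |
| 1.68 | 0.114 | 34% | 34% |
| 1.40 | 0.113 | 17% | 18% |

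If 20% and 10% are instead risks standardised over the confounders, simulated adjusted power under positive confounding was about 68% to 77%, which is close to or above the unadjusted 71%. Under negative confounding it was 58% to 69%.

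**The case against.** The strongest reply is that the documents do not fix the adjustment loss. They give no R², diagram or covariate list, and a minimal adjustment set may be small. At R² of 0.05 to 0.10 the loss is only 2 to 4 points (70.7% to 68.8% or 66.8%). Figures near 60% need an R² of 0.20 or more, which nothing in the protocol supports. The simple variance correction also describes covariates that predict CKD without counting any effect they have on the outcome, whereas real confounders affect both. The protocol never calls its two rates crude, and if they are standardised risks, power need not fall. All of this stands. A reader might infer that the adjusted test must have lower power, or that its power is some particular figure such as 58%. The documents do not support either.

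It is also fair to say that sizing a cohort on an unadjusted contrast is common, and that the larger demonstrable error is pairing 548 with 80%. That too stands, but it does not rescue the sentence. The claim of adequate power for an independent effect is printed in the protocol, and its printed inputs do not deliver it, even before adjustment. This is therefore not an omission that a separate analysis plan could fill.

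**Conclusion.** The point holds as a mismatch between the calculation and the claim made from it. The calculation contains nothing for adjustment, and under its own inputs 548 initiators give about 71% power for the unadjusted comparison, some 9 points below the stated 80%. That part needs no outside assumption beyond the usual pooled formula; the Wald version gives 73%.

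Further loss from adjustment is expected if the covariates predict CKD, but it is not certain. It is 2 to 13 points for R² of 0.05 to 0.30 with the effect held fixed. It is far more if the 20% versus 10% contrast is partly positive confounding, and there may be none if the rates are already standardised. The protocol does not say which case applies, so it cannot claim adequate power for the adjusted effect. Nor does it follow that the study must enrol more people; that would be so only if 80% power is to be kept.

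**What to change.** In the Sample size calculation:

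1. Restate the power at 548 as about 71% for the unadjusted CKD comparison, or give the method and inputs that lead to 548 at 80%. Labelling the present figures as unadjusted would not be enough, because the pairing of 548 with 80% would still be wrong.
2. Say whether 20% versus 10% is a crude or an adjusted contrast.
3. Replace the sentence on an independent risk factor with the adjusted power at 548 over a stated range of R² (for example 0.05 to 0.30), or drop the adequacy claim.
4. Say that the adjusted odds ratio will be reported with its confidence interval, and that a non-significant result will not be taken as absence of an independent effect.

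This costs a few sentences and a less favourable power statement. No further participants or data are needed if the power is restated. If the sponsor prefers to keep 80%, the unadjusted comparison alone needs 709 initiators, or 709/0.40 = 1,773 enrolled (rounded up), before any allowance for adjustment.

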Building a prospective cohort to collect clinical information on LTBI‑positive individuals is needed to establish a research platform for answering these questions. In this manuscript, we provide an overview of the design, methods and scope of this cohort study. This Safety of Preventive Treatment in People at Risk for Tuberculosis (STEP-TB) study is supported by the Korea National Institute of Health as a national research project. The study findings and datasets will be used as scientific evidence for developing the national TB control master plan in accordance with the TB Prevention Act. We aim to provide evidence to inform national TB policy by evaluating the safety of TPT in the high‑risk groups for active TB disease.

Among the medical high-risk groups for TB, including individuals with chronic kidney disease (CKD), chronic lung disease, diabetes mellitus, malignancy, immunosuppressive conditions, and occupational exposure, the safety of TB preventive treatment remains an important clinical concern. CKD is of special interest because patients with CKD have an increased risk of TB and may be more vulnerable to drug-related adverse events. This study aims to evaluate the safety of TPT in individuals at high risk of developing active TB disease in Korea using a multicenter prospective cohort design. The primary objective is to specifically investigate whether CKD is associated with an increased risk of adverse events during TPT. The secondary objective is to assess the association between CKD and TPT completion, to describe the TPT cascade of care among individuals at high risk of TB, and to evaluate the preventive effectiveness of TPT in reducing progression to active TB during the follow-up period. These objectives will allow a comprehensive understanding of both the safety and effectiveness of TPT in high-risk populations.

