CKD is an important high-risk condition that warrants inclusion in this study because it is consistently associated with a markedly increased risk of TB [12], largely driven by reactivation of latent infection rather than new exposure. As renal function declines, particularly in patients approaching or receiving dialysis, immune dysregulation substantially increases the likelihood of progression from LTBI to active TB disease, with reported TB incidence in dialysis populations far exceeding that of the general population [13]. In addition, TB in patients with CKD often presents atypically, leading to delayed diagnosis, poorer outcomes, and increased risk of transmission within dialysis units, thereby posing both individual and public health concerns [14]. Despite these risks, LTBI screening and treatment practices in CKD remain highly variable, largely due to diagnostic uncertainty and concerns about treatment-related adverse events, and robust, condition-specific safety data are lacking [15,16]. Recent reviews [17] have highlighted the urgent need for prospective evidence to better define the balance of benefit and harm of LTBI treatment in CKD populations and to support more consistent, evidence-based preventive strategies. By including patients with CKD across disease stages, the STEP-TB cohort is well positioned to address these critical evidence gaps and inform safer, more effective LTBI management in this high-risk group.

Importantly, this study is also designed to examine the cascade of care for LTBI [18,19], from diagnostic testing and treatment initiation to treatment completion, across different comorbidity groups. By systematically evaluating barriers and drop-offs at each step of the LTBI care continuum, STEP-TB will identify condition-specific hurdles faced by patients with complex medical comorbidities. Understanding these real-world challenges is essential for informing feasible and safe expansion of LTBI treatment policies, and the evidence generated by this cohort will directly support efforts to broaden preventive treatment strategies while maintaining patient safety.

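### Recruitment is fixed only as a total of 1,370 testing candidates; nothing ties it to the number of CKD treatment initiators, which largely sets the power of the primary comparison

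*Protocol article*

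**What the plan says.** The Introduction sets the primary question: "The primary objective is to specifically investigate whether CKD is associated with an increased risk of adverse events during TPT". The section Sample size calculation gives the inputs. It expects that "approximately 40% of individuals undergoing LTBI testing will be LTBI-positive and initiate TPT, of whom about 15% will have CKD". It continues: "Assuming adverse event rates of 20% in the CKD group and 10% in the non-CKD group", and concludes that "a total of 548 TPT initiators will be required to detect this difference with a two-sided α of 0.05 and 80% power".

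That number of initiators is then converted to enrolment, in a sentence cut short here: "Based on an expected LTBI positivity rate of 40%, approximately 1,370 LTBI testing candidates need to be enrolled to yield a sufficient number of treatment". The recruitment statement that follows is "A total target enrollment of 1,370 participants is planned, with competitive enrollment implemented across participating sites", with per-site targets that may be adjusted.

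The section Study design, and setting allows further sites to be added for capacity and lets enrolment run to 31 December 2027. Neither is linked to CKD. In Table 1, CKD is one of many qualifying conditions, and the article states no minimum or quota for any of them.

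**The concern.** In a comparison of two groups of very unequal size, the smaller group carries most of the uncertainty. Here that is the CKD group, expected to be "of whom about 15% will have CKD". The article fixes the number of people tested, which is two steps removed: a person must test positive and start treatment, and must also have CKD. Each step rests on an assumed proportion, and the article ties no target, count or adjustment to the result.

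The study could therefore reach 1,370 enrolled and still have too few CKD initiators to answer its primary question. The printed 80% power gives the reader no warning, because even the expected CKD count does not deliver it.

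**Working it through.** **Inputs**, all from Sample size calculation: p₁ = 0.20 (CKD), p₀ = 0.10 (non-CKD), two-sided α = 0.05, power 80%, 548 initiators, 40% positive and initiating, 15% of these with CKD.

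**The plan's own figures.** The conversion 548 / 0.40 = 1,370 reproduces. The 548 does not. For the pooled two-proportion test at 15:85, k = 0.85/0.15 and p̄ = 0.15 × 0.20 + 0.85 × 0.10 = 0.115:

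n₁ = [1.96 √(p̄(1−p̄)(1+1/k)) + 0.842 √(p₁(1−p₁) + p₀(1−p₀)/k)]² / (p₁−p₀)² ≈ 106.3, so 107 CKD. The total is 107 / 0.15 ≈ 714, and enrolment is 714 / 0.40 = 1,785.

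Other two-sided formulas at 15:85 give totals of 654 (Wald log-odds), 709 (logistic with a binary covariate), 765 (arcsine), 787 (continuity-corrected) and 920 (unpooled). None gives 548.

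**Expected CKD count.** 1,370 × 0.40 × 0.15 = 82.2, which leaves 466 non-CKD initiators of 548.

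**Power at that count.** Power = Φ[(|p₁−p₀| − 1.96 s₀) / s₁], where s₀ is the pooled standard error under no difference and s₁ the unpooled one.
- p̄ = (82 × 0.20 + 466 × 0.10) / 548 = 0.115
- s₀ = √(0.115 × 0.885 × (1/82 + 1/466)) = 0.0382
- s₁ = √(0.16/82 + 0.09/466) = 0.0463
- Power = Φ[(0.10 − 0.0749) / 0.0463] = Φ(0.543) ≈ 0.71

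Simulation at 82 v 466 gives 0.70 for both the chi-square test and the Wald test from logistic regression.

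**Which group matters.** The variance parts in s₁² are 0.16/82 = 0.00195 (CKD) and 0.09/466 = 0.00019 (non-CKD), so CKD contributes 91%. With 55 CKD initiators, raising the non-CKD group from 493 to 5,000 moves power only from 59% to 64%.

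**Chance alone.** If 40% and 15% are exactly right, the CKD count follows Binomial(1,370, 0.06), with a 95% range of 65 to 100.

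**Power by CKD count, 548 initiators held fixed.** Shares other than 15% are assumptions.

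| CKD initiators | Share | Power |
|---|---|---|
| 55 | 10% | 59% |
| 65 | lower chance limit | 64% |
| 66 | 12% | 64% |
| 82 | 15% (plan) | 71% |
| 100 | upper chance limit | 76% |
| 110 | 20% | 78% |
| 118 | 21.5% | 80% |
| 137 | 25% | 83% |

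**The 40%.** The section uses 40% first for people who test positive and initiate, then as the positivity rate, although Table 2 has a positive group without TPT. If 40% is positivity only and 80% of positives start (an assumption), there are 438 initiators, 66 of them with CKD, and power is 62%.

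**The case against.** **Much of the shortfall belongs to the 548.** This stands. The drop from 80% to 71% at exactly 15% arises because 548 is too small at 15:85. With 714 initiators from 1,785 enrolled, chance alone gives 88 to 127 CKD initiators and power of about 74.8% to 84.5%, which is ordinary sampling variation. What remains is that a corrected total would still rest on an assumed 15% with no check on it.

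**A condensed article may leave accrual tracking to the full protocol.** This is fair, and the point does not rest on missing operational detail. It rests on what the article does fix: a recruitment target in a unit that does not secure the primary comparison, and a power figure that the target does not deliver.

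**Stronger readings that the article does not support.**
- A reader might infer that enrolment closes at 1,370 whatever the CKD count. No closing rule is printed; there is a planned total, a calendar end, adjustable site targets and possible extra sites.
- A reader might blame competitive enrolment. It leaves the case mix to whichever sites recruit fastest, but the cause is the absence of a CKD target.
- A reader might conclude that the share will fall below 15%, because the Discussion says that "LTBI screening and treatment practices in CKD remain highly variable, largely due to diagnostic uncertainty and concerns about treatment-related adverse events". This is weak evidence. The 15% is already stated among initiators, the Discussion's remark on deferring treatment concerns complex comorbidity in general, and no figure supports a lower share. The share could equally be higher.

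**Steering recruitment to CKD is a trade-off.** This also stands. The cohort is meant to describe real-world care across many risk groups, so passive accrual is defensible. Nor is 118 of 548 free. At a 40% yield it needs 118 / 0.40 = 295 CKD enrollees. At an assumed 30% yield it needs about 393, total initiators fall to about 509 and power to 79%. At 20% it needs 590, with 430 initiators and 77%.

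**Conclusion.** The point holds in a limited form. The recruitment target is expressed only as a total of testing candidates, and no recruitment lever in the article is tied to the CKD initiator count. On the plan's own assumptions that count is about 82 (chance range 65 to 100), and power is about 71% (64% to 76%) rather than 80%. At an assumed 10% share it is about 59%.

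These figures rest on the 20% and 10% rates, an unadjusted pooled two-proportion test at two-sided 0.05, and 548 initiators. The article does not show that the share will be below 15%. The change is worth making because it is cheap and replaces a power figure that the design does not deliver.

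**What to change.** In Sample size calculation:

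1. State the recruitment target as CKD TPT initiators as well as the total, from a corrected calculation. At a 15% share this is about 107 CKD of 714 initiators, or about 1,785 enrolled at 40%. If the total stays at 548 initiators, it is about 118 CKD.
2. Have the study coordination centre, which the Ethics section already charges with data monitoring, track the CKD initiator count during enrolment.
3. If the planned 1,370 is kept, restate power at the CKD count achievable within it: about 71% at 82.

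Directing site effort toward CKD referrals within the total is optional. It reaches 80% only if CKD patients initiate at about the assumed 40%. The cascade of care would then need reporting by CKD stratum, or reweighting to the natural mix.

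Stating the target, tracking the count and restating power cost a wording amendment and routine counting, with no extra participants. Restoring 80% at a 15% share costs about 1,785 − 1,370 = 415 further enrollees. Steering instead may slow the last part of recruitment, and whether the hospitals can supply about 295 or more CKD enrollees is not known from the article.

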### Ethics

This study will be conducted in accordance with the principles of the Declaration of Helsinki and the Good Clinical Practice guidelines. The study protocol has been reviewed and approved by the Institutional Review Board of Catholic Medical Center, The Catholic University of Korea (Approval number; XC25ENDI0053). This approval covers all participating sites in this multi-center study under a centralized institutional review board review process; therefore, no additional site-specific ethics approvals were required. Any major protocol amendments will be submitted for additional IRB approval prior to implementation.

Written informed consent will be obtained from all participants before enrollment. During the consent process, participants will receive detailed information regarding the study objectives, procedures, potential risks, and confidentiality safeguards. They will also be informed that participation is voluntary and that they may withdraw from the study at any time without any impact on their clinical care.

All participant data will be de-identified and managed using a secure, password-protected database. Only authorized research personnel will have access to identifiable information, and data handling will comply with the Personal Information Protection Act of the Republic of Korea. Data quality and consistency will be regularly monitored by the study coordination center.

